### Statistical analysis

All analyses will be performed according the intention-to-treat principle. Descriptive statistics will be used to present demographic and baseline characteristics. Between- group differences in the primary and secondary endpoints will be analysed by the unpaired T-test for continuous variables and by a chi squared test for categorical variables. A paired T-test will be used to evaluate within-group differences for the primary endpoint.

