### Randomisation, blinding and treatment allocation

Participants are randomly allocated to the intervention or control group (1:1) after reaching stable HF and completing the first measurements. Participants will be replaced when discontinuing from study protocol before randomisation. Randomisation is performed by the investigator using a computerised randomisation system in the web-based database software Castor EDC (Castor Electronic Data Capture, Ciwit BV, Amsterdam, The Netherlands). The computer system uses variable block sizes (2,4) stratified for age (< 75 years or ≥ 75 years) and left ventricular ejection fraction (LVEF ≤ 40%, LVEF 41 – 49% or LVEF ≥ 50%) for randomisation. Overall, patients with HF are elderly with an average age of 75.2 years in Western Countries as presented by Norhammar et al. [33]. The participants, investigator, and other medical professionals will not be blinded for the treatment allocation due to the nature of the intervention. For the assessment of the functional tests (Short Physical Performance Battery and Handgrip Strength test) a blinded investigator will be involved.

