### Physical functional capacity

Physical functional capacity is assessed with the Short Physical Performance Battery (SPPB) functional test. The SPPB is an objective assessment tool to evaluate the lower extremity function in older persons to reflect the physical self-reliance. It is described as a screening tool to detect frailty [38], and a predictor of major adverse health-related events (e.g. disability, hospitalisation and mortality) in elderly patients [39–41]. The test consists of three parts: gait speed, standing balance and time to rise from a chair. Each test is scored out of 4 points; 0 corresponds with not able to perform the test, and 4 with best performance. A maximum of 12 points can be scored, 0–3 corresponding with severe physical limitation, 4–9 high risk, and 9–12 low risk for developing new physical limitations.

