### Readmission rate and other adverse events

The readmission rate and other adverse events are assessed during the study period in both groups. Readmission is defined as a hospitalisation for at least 24 h. We will differentiate between HF related causes, other cardiovascular causes, and non-cardiovascular causes of readmission. Other adverse events that will be reported are: 1) acute decompensation without hospital admission, 2) myocardial infarction, 3) emergency room visit without hospitalisation, 4) (cardiac) surgery, 5) admission to a nursing home or rehabilitation centre, 6) (cardiovascular) death, and 7) adverse events that might be related to the intervention.

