### Sample size calculation

The sample size calculation is based on the primary outcome measurement – physical functional capacity assessed by the SPPB. Assuming that the study population in general corresponds with lower performance (SPPB score ≤ 9), and that CTR will result in an increase of 1.6 points (SD 2.17) as described by Rengo et al., 64 patients are needed to achieve a statistical power of 0.80 [57]. Previous research found a subjective and quantitative better physical functional capacity with an increase of 0.4 – 1.5 points [58].

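### The unpaired t-test named for SPPB ignores baseline and the randomisation strata and, on observed scores, drops randomised patients without a score; a longitudinal mixed model would serve the stated intention-to-treat aim better

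*Protocol article*

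**What the plan says.** All places are in the protocol article.

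- **Statistical analysis:** "All analyses will be performed according the intention-to-treat principle". For comparisons of the two arms, on SPPB and every other endpoint, the section says that these "will be analysed by the unpaired T-test for continuous variables and by a chi squared test for categorical variables". Within-group change in SPPB gets a paired t-test.
- **Outcome measures:** SPPB is measured at randomisation, 18 weeks and 6 months.
- **Physical functional capacity:** each of the three SPPB components is scored from 0 to 4, and "0 corresponds with not able to perform the test".
- **Randomisation, blinding and treatment allocation:** allocation is 1:1, stratified by age (two levels) and LVEF (three levels), after the first measurements are complete. "Participants will be replaced when discontinuing from study protocol before randomisation"; nothing is said about replacement afterwards.
- **Sample size calculation:** for an increase of 1.6 points with SD 2.17, "64 patients are needed to achieve a statistical power of 0.80". The Abstract gives the same 64 as the number to be recruited. No alpha, sidedness or loss allowance is stated.

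**The concern.** The stated principle is to analyse patients as randomised. The test named for the primary outcome needs a score from each patient it compares, so on observed data it is a complete-case comparison at each visit. It would be unbiased only if, within each arm, the patients with no score resembled those with one.

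The article gives reasons to doubt this. It describes SPPB as a predictor of disability, hospitalisation and mortality, so patients who die or deteriorate are likely to be low scorers. Death is among the events to be reported. The Limitations section concedes that the programme may be too demanding for the intervention group, so loss might differ by arm. If more low scorers are lost from the control arm, a benefit is understated; if more are lost from the CTR arm, it is overstated.

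The second cost is precision. Baseline SPPB and the two stratification factors are known for everyone randomised, yet the named test has no place for the strata, and none for baseline unless change scores are compared.

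**Working it through.** **1. What the named test uses**

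| Information collected | Unpaired t-test at one visit | Mixed model over both follow-up visits |
|---|---|---|
| SPPB at that visit | yes | yes |
| SPPB at the other follow-up visit | no | yes |
| Baseline SPPB | only if change scores are tested | yes, as covariate |
| Age and LVEF strata | no | yes |
| Patient missing one follow-up visit | dropped at that visit | kept |

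The article does not say whether scores or changes are compared. Let ρ be the correlation between baseline and follow-up SPPB, with equal variances. Relative to comparing raw follow-up scores, the variance of the treatment difference is multiplied by 2(1 − ρ) for change scores and by (1 − ρ²) = (1 − ρ)(1 + ρ) with baseline adjustment. Since 1 + ρ ≤ 2 and 1 − ρ² ≤ 1, adjustment is never less precise than either form, apart from the degree of freedom spent. The article gives no ρ, so the gain cannot be put in figures.

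**2. Bias from complete cases**

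If k of n patients in an arm are unobserved and lie on average g points below that arm's mean, the observed mean is too high by k·g/(n − k). The bias in the treatment difference is the CTR value minus the control value. The article gives neither k nor g for either arm, so neither sign nor size can be derived.

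**3. The planned sample size**

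Inputs: δ = 1.6 and σ = 2.17 (Sample size calculation), taken as a between-group difference and its SD; 1:1 allocation; power 0.80. Two-sided alpha 0.05 is an assumption.

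- Normal approximation: n per arm = 2(1.960 + 0.842)² × (2.17/1.6)² = 2 × 7.85 × 1.839 = 28.9, so 29 per arm, 58 in total.
- Exact (noncentral t): 30 per arm, 60 in total, power 0.802.
- One-sided 0.05 would need 46 (normal) or 48 (t).

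None of these returns 64 exactly. An unstated allowance would: 60/0.94 = 63.8, or 58 × 1.10 = 63.8, each rounding up to 64.

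**4. Power of the planned t-test when some of the 64 are unobserved**

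The noncentrality is δ/(σ√(2/n)), with n analysed per arm and losses split evenly. For n = 32 it is 1.6/(2.17 × 0.25) = 2.95.

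| Analysed (of 64) | Loss | Power, t | Power, normal |
|---|---|---|---|
| 64 | 0% | 0.827 | 0.839 |
| 60 | 4 patients (6.25%) | 0.802 | 0.815 |
| 58 | 6 patients (9.4%) | 0.788 | 0.802 |
| 57.6 | 10% | 0.785 | 0.799 |
| 51.2 | 20% | 0.734 | 0.751 |

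The surplus over 60 is four patients by the t calculation. By the normal approximation it is six over 58.

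**The case against.** The strongest reply is that this is a short statistics section in a journal article. Rules for missing scores and deaths are commonly left to the full protocol or SAP, and neither is shown. Intention-to-treat in its basic sense means analysis in the allocated arm, and a t-test can follow imputation or an assigned score. That stands: complete-case use is inferred, not stated, and the absence of a missing-data rule is not itself a fault here. It does not rescue the choice of test, which the article does fix and which has no place for the strata or the other follow-up visit even when every score is present.

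Four stronger readings are tempting and are not supported:

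- *That the t-test flatly contradicts intention-to-treat.* It would do so only if no further rule exists, and that cannot be known from the article.
- *That patients admitted to nursing homes drop out.* The article lists "admission to a nursing home or rehabilitation centre" only as an event to be reported. It does not end participation or SPPB testing, and inability to perform a component already scores 0.
- *That power falls below 0.80.* With 64 analysed it is 0.827. The article gives no loss rate after randomisation, and 64 may already contain a small unstated allowance.
- *That the bias is some particular number of points.* For example, losing 5 of 32 controls and 2 of 32 CTR patients, each 3 points below their arm mean, gives 2 × 3/30 − 5 × 3/27 = −0.36. Every input to that figure is invented, so it says nothing about the size or direction of bias in this trial.

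It is also fair to say that a patient who finds CTR too demanding may stop the programme and still attend the SPPB visit. The Limitations section lists measures to reduce the burden.

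**Conclusion.** The point holds as a criticism of the chosen method. On observed scores, the unpaired t-test excludes randomised patients without a score at that visit and leaves prognostic information unused. It is less precise than an adjusted longitudinal analysis of data the trial already collects, and open to bias if loss depends on function or differs by arm. The size and direction of that bias are unknown.

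On power, the stated 0.80 is met as long as no more than about 6% of the 64 (4 patients) are unobserved by the t calculation, or about 9% (6 patients) by the normal approximation. At an assumed 10% to 20% loss, t-test power is 0.79 to 0.73. These figures rest on two-sided 0.05, on 1.6 points being a between-group difference with SD 2.17, and on losses split evenly between arms. This is worth changing before analysis, but it does not show that the trial is underpowered.

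**What to change.** 1. Replace the unpaired t-test for SPPB with a longitudinal mixed model: outcomes at 18 weeks and 6 months, treatment, visit and treatment-by-visit, adjusted for baseline SPPB and the age and LVEF strata. Estimate the between-group contrast from all randomised patients with data. With baseline as a covariate, a patient with neither follow-up score adds nothing to the contrast, so report the number of such patients by arm.
2. Keep the existing scoring rule: a patient who attends but cannot perform a component scores 0 on it.
3. Add one sensitivity analysis that gives patients who die the worst SPPB score.
4. In the sample size section, state alpha and sidedness, and give power under an assumed loss, for example 0.79 at 10% and 0.73 at 20% for the planned t-test. If 60 evaluable patients are to be protected, the number to randomise is 60/0.90 = 66.7, so 67, at 10% loss, or 60/0.80 = 75 at 20% (68 and 76 for equal arms).
5. If the full protocol or SAP already has a missing-data rule, align it with this model.

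Items 1 to 3 cost wording and a little analysis work, with no extra visits or patients; item 4 adds patients only if the sponsor chooses to protect the 60. The downside is that the model assumes scores are missing at random given the data in the model. The worst-score analysis probes that assumption for deaths but does not remove it.

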### Outcome measures

The primary outcome measure is physical functional capacity at randomisation, 18 weeks and 6 months after randomisation. Secondary outcome measures are recovery after submaximal exercise, maximal exercise capacity, subjective health status and quality of life, personality and behaviour aspects, nutrition behaviour, compliance and acceptance to the intervention, fluctuation of congestive HF biomarkers, and readmission rate.

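### The primary SPPB comparison is an unadjusted t-test with within-arm paired tests beside it; adjusting for baseline SPPB and the randomisation strata would gain precision at almost no cost

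*Protocol article*

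**What the plan says.** All of the following is in the protocol article.

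- **Between-arm test (Statistical analysis).** "Between- group differences in the primary and secondary endpoints will be analysed by the unpaired T-test for continuous variables". No covariate is named there or elsewhere. The section does not say whether the quantity tested is the follow-up score or the change from randomisation.
- **Within-arm test (same section).** "A paired T-test will be used to evaluate within-group differences for the primary endpoint".
- **Baseline is measured (Outcome measures).** "The primary outcome measure is physical functional capacity at randomisation, 18 weeks and 6 months after randomisation". Every randomised patient should therefore have an SPPB score from before the intervention.
- **Stratified allocation (Randomisation, blinding and treatment allocation).** "The computer system uses variable block sizes (2,4) stratified for age (< 75 years or ≥ 75 years"), together with "left ventricular ejection fraction (LVEF ≤ 40%, LVEF 41 – 49% or LVEF ≥ 50%) for randomisation". That is 2 × 3 = 6 strata.
- **Planning values (Sample size calculation).** "CTR will result in an increase of 1.6 points (SD 2.17"), with 64 patients for power 0.80. The text does not say whether 2.17 is the SD of a score or of a change. Alpha, sidedness and dropout are not given.

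**The concern.** The design spends effort on balancing age and LVEF and on measuring SPPB before allocation, and the stated test then uses none of this as a covariate. With 64 patients, baseline adjustment is the cheapest precision available. It also corrts for chance imbalance in baseline SPPB, which small blocks within age and LVEF strata do not control directly.

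The within-arm paired tests are a second, smaller matter. The stated hypothesis is that CTR plus RPM is superior to RPM alone. A p-value for change inside one arm cannot test that, because any gain common to both arms counts towards it. Placed beside the randomised comparison on the primary endpoint, such p-values are easy to misread.

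**Working it through.** **Inputs.** Difference 1.6 and SD 2.17 (Sample size calculation); 32 per arm (64 patients, 1:1). Assumed because the article does not give them: two-sided alpha 0.05, no dropout, and the baseline-to-follow-up correlation r of SPPB, with equal SDs at both times.

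**1. The plan's own figure.** Normal approximation: n per arm = 2 × (1.96 + 0.84)² × (2.17/1.6)² ≈ 28.9, so 29 per arm and 58 in total. The exact t-test needs 29.87, so 30 per arm and 60 in total. The stated 64 is not reproduced from the stated inputs alone, but it lies on the safe side. With 32 per arm the noncentrality is 1.6 / (2.17 × √(2/32)) = 2.95, and the unpaired t-test has power 0.83.

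**2. ANCOVA power at 32 per arm.** The residual SD depends on what 2.17 describes:

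- SD of change: residual SD = 2.17 × √((1 + r)/2).
- SD of the score: residual SD = 2.17 × √(1 − r²).

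| r | 2.17 = SD of change: residual SD | power | 2.17 = SD of score: residual SD | power |
|---|---|---|---|---|
| 0.3 | 1.75 | 0.95 | 2.07 | 0.86 |
| 0.5 | 1.88 | 0.92 | 1.88 | 0.92 |
| 0.7 | 2.00 | 0.88 | 1.55 | 0.98 |
| 0.9 | 2.12 | 0.85 | – | – |

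The comparator is 0.83 in both cases: a t-test on change in the first, a t-test on follow-up scores in the second. In patients, ANCOVA needs a fraction (1 + r)/2 of the N of a t-test on change, and 1 − r² of the N of a t-test on follow-up scores. At r = 0.5 both are 0.75.

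The table spends one degree of freedom on baseline. Adding one for age and two for LVEF leaves 64 − 6 = 58 residual degrees of freedom and changes power by about 0.001.

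**3. Ignoring the strata.** Null trials of 64 patients were simulated with stratified blocks of 2 and 4 in six strata. Stratum sizes were assumed, and the outcome differed between two halves of the strata. The unadjusted t-test rejected in 4.3%, 2.8% and 1.9% of trials when strata explained 10%, 20% and 30% of the variance, against a nominal 5%. The test is conservative, to the extent that the strata predict SPPB.

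**4. Within-arm tests.** Suppose both arms gain the same amount g, with change SD 2.17 and 32 per arm. Let p be the chance that one arm's paired test shows a significant gain (noncentrality g / (2.17/√32)). The chance that CTR is significant and control is not is p × (1 − p).

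| Shared gain g | p | CTR significant, control not |
|---|---|---|
| 0 | 0.025 | 2.4% |
| 0.2 | 0.073 | 7% |
| 0.4 | 0.171 | 14% |
| 0.8 | 0.524 | 25% |
| 1.0 | 0.714 | 20% |
| 1.5 | 0.966 | 3% |

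A valid two-sided 5% between-arm test wrongly favours CTR in 2.5% of trials.

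**The case against.** The strongest reply is that nothing here is broken. On the article's own inputs the unpaired t-test is valid and exceeds its stated power of 0.80. That stands, and it limits the point to efficiency.

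Four stronger readings are tempting, and the article supports none of them.

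- **That the plan ignores baseline altogether.** The sample size section speaks of an increase, which may mean that change is tested. A test on change uses baseline, only not optimally, and at high correlation ANCOVA then adds little (0.85 against 0.83 at r = 0.9).
- **That leaving out the strata risks a false positive.** It works the other way: the test becomes conservative.
- **That the trial will claim an effect from the paired tests.** The article gives them only the task of evaluating within-group differences, and its hypothesis is explicitly between-arm. Harm would need a later misreading.
- **That both arms are bound to improve after randomisation.** The article does not say so. Patients are randomised only after optimal medical therapy and at least two weeks of unchanged symptoms, so some early recovery comes before the baseline measurement. The shared gain is an assumption, and no single percentage from the last table should be quoted alone.

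It can also be said that an article leaves covariates and the choice of score to an analysis plan. That has some force for the choice of score. It has less for the test itself, because the article does name a method for the primary endpoint and it is an unadjusted one.

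**Conclusion.** The point holds as an avoidable loss of precision. If the 1.6-point difference and SD of 2.17 are right and all 64 patients are analysed, moving from the t-test to ANCOVA raises power from 0.83 to between 0.85 and 0.95 (2.17 as SD of change, r from 0.9 down to 0.3), or to between 0.86 and 0.98 (2.17 as SD of the score, r from 0.3 up to 0.7). The size rests on a correlation that the article does not give, but the direction is the same throughout these ranges. Omitting the strata widens the error bars somewhat if age and LVEF predict SPPB.

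The within-arm p-values add nothing to the test of superiority. If read as evidence of effect, they would mislead in about 2% to 25% of trials for a shared gain of 0 to 1.5 points. A reader should not infer that the primary test is invalid, that the sample size has failed, or that the investigators plan to rely on the paired tests. Severity: should-fix.

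**What to change.** - Make the primary analysis an ANCOVA of follow-up SPPB on arm, baseline SPPB, age stratum (2 levels) and LVEF stratum (3 levels). Report the adjusted difference with its 95% CI. This also settles the open choice of score, because with baseline in the model the estimated arm effect is the same for follow-up and for change.
- Use the same baseline-adjusted form for continuous secondary outcomes that have a value at randomisation.
- Replace the paired t-tests by descriptive within-arm changes without p-values.

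The cost is a few lines in the analysis section and four model degrees of freedom (one for baseline, one for age, two for LVEF). No new data and no extra patients are needed. The change should be fixed before outcome data are analysed.

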### Sample size calculation

The sample size calculation is based on the primary outcome measurement – physical functional capacity assessed by the SPPB. Assuming that the study population in general corresponds with lower performance (SPPB score ≤ 9), and that CTR will result in an increase of 1.6 points (SD 2.17) as described by Rengo et al., 64 patients are needed to achieve a statistical power of 0.80 [57]. Previous research found a subjective and quantitative better physical functional capacity with an increase of 0.4 – 1.5 points [58].

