**Methods:**

In this randomised controlled trial, 64 CHF patients will be recruited during hospitalisation for acute decompensated heart failure, and randomised to CTR combined with remote patient management (RPM) or RPM alone (1:1). All participants will start with RPM after hospital discharge for early detection of deterioration, and will be up titrated to optimal medical therapy before being randomised. CTR will start after randomisation and consists of an 18-week multidisciplinary programme with exercise training by physical and occupational therapists, supported by a (remote) technology-assisted dietary intervention and mental health guiding by a physiologist. The training programme consists of three centre-based and two home-based video exercise training sessions followed by weekly video coaching. The mental health and dietary programme are executed using individual and group video sessions. A wrist-worn device enables remote coaching by the physical therapist. The web application is used for promoting self-management by the following modules: 1) goal setting, 2) progress tracking, 3) education, and 4) video and chat communication. The primary outcome measure is physical functional capacity evaluated by the Short Physical Performance Battery (SPPB) score. Secondary outcome measures include frailty scoring, recovery after submaximal exercise, subjective health status, compliance and acceptance to the rehabilitation programme, and readmission rate.

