### Limitations

This study has a number of limitations. First, with the use of a digital intervention, participants with insufficient digital literacy are excluded which may lead to a selection bias. However, this effect is expected to be limited through the involvement of caretakers and home care organisations at inclusions and follow-up. Furthermore, one of our previous studies with a similar intervention has already shown feasibility of such a digital intervention in elderly CHF patients [31] and improvements have been made to the programme in response to patient experiences and feedback on this previous intervention. Finally, elderly people have significantly increased their digital skills over the past decade, making it highly likely that they will be able to use the digital intervention, and that future implementation of this programme will be successful [65].

Second, due to the comprehensiveness of this CTR intervention, participation may be too demanding for the patients in the intervention group. In the design of the care pathway, this potential burden has been dealt with by: 1) individualising the program and consultation frequency to the patient’s needs, 2) involving caretakers, 3) regularly monitoring the patient’s progress and adjust if necessary, 4) using video consultation to limit clinical appointments, and 5) adjusting the platform with the feedback from the previous study.

A final limitation is that the control group will not receive CTR in the first period after hospital discharge. However, the referral rate in the CHF population is still generally low, especially for those who were admitted recently or are classified as frail. In this study, all participants will be offered CR eventually; the intervention group during the study period and the control group after finishing the follow-up period. Furthermore, this study is expected to increase awareness on benefits of CR and will therefore hopefully improve the referral rate.

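### The 64 patients stated for power 0.80 do not follow from the stated inputs and t-test (60 complete patients suffice), and the text does not show how much loss 64 tolerates

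*Protocol article*

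**What the plan says.** The Sample size calculation section assumes that "CTR will result in an increase of 1.6 points (SD 2.17"), taken from a cited earlier study, and concludes that "64 patients are needed to achieve a statistical power of 0.80". It gives no alpha, no sidedness and no loss rate.

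The other inputs stand elsewhere in the protocol article:

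- **Test.** Under Statistical analysis, between-group differences in the endpoints "will be analysed by the unpaired T-test for continuous variables".
- **Allocation.** "Participants are randomly allocated to the intervention or control group (1:1"), under Randomisation, blinding and treatment allocation.
- **Number recruited.** The Abstract says that "64 CHF patients will be recruited during hospitalisation for acute decompensated heart failure", the same figure as the number needed.
- **Replacement.** "Participants will be replaced when discontinuing from study protocol before randomisation". Nothing is said about replacing patients lost afterwards.
- **Timing.** "The primary outcome measure is physical functional capacity at randomisation, 18 weeks and 6 months after randomisation".

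**The concern.** A sample size statement should let a reader get from the inputs to the number. Here the inputs and the named test lead to a smaller number than 64, so 64 either includes a margin that is not described or comes from a different calculation. The reader cannot tell which, and the difference matters: if 64 is the number to be analysed, nothing is left for loss; if it is an inflated number, the loss it was meant to cover is unknown.

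The population makes this more than a formality. Patients are recruited during an admission for decompensated heart failure, frail elderly patients are not excluded, and follow-up runs to 6 months after randomisation. Death and nursing home admission are among the events to be recorded. The Limitations section accepts that "participation may be too demanding for the patients in the intervention group", so loss could also differ between the arms. Analysis by intention to treat does not by itself supply a missing SPPB score.

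**Working it through.** **Inputs.** Difference 1.6 and SD 2.17 (Sample size calculation); unpaired t-test (Statistical analysis); 1:1 allocation; power 0.80. Assumed: two-sided alpha 0.05, and 1.6 as the difference between the arms. The standardised difference is d = 1.6 / 2.17 = 0.737.

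**Step 1: try to reproduce 64.**

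Normal approximation, per arm: n = 2 × (1.960 + 0.8416)² × (2.17 / 1.6)² = 2 × 7.849 × 1.839 = 28.87, so 29 per arm, **58** in total.

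Exact t-test (noncentral t, 2n − 2 degrees of freedom, noncentrality d × √(n/2)): n = 29.87, so 30 per arm, **60** in total.

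| Per arm | Total | Power, exact t | Power, normal |
|---|---|---|---|
| 29 | 58 | 0.788 | 0.802 |
| 30 | 60 | 0.802 | 0.815 |
| 32 | 64 | 0.827 | 0.839 |

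Other choices of alpha or power with the same test do not give 64 either: one-sided 0.05 needs 48, two-sided 0.025 needs 74, and two-sided 0.05 with power 0.85 needs 70.

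**Step 2: routes that do reach 64.** Each uses something the article does not state.

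- A 10% multiplier on the normal-approximation result: 58 × 1.10 = 63.8.
- About 6% loss on the exact result: 60 / 0.94 = 63.8.
- About 8% loss on the normal-approximation result: 58 / 0.92 = 63.04, rounded up to 64.
- A rank test with relative efficiency 0.955: 29.87 / 0.955 = 31.3, so 32 per arm. On this route 64 would contain almost no allowance for loss.

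**Step 3: the margin in 64.** By the exact t-test, 64 − 60 = 4 patients may lack the endpoint (4 / 64 = 6%). With 4 missing, power is 0.802 if split 30/30 and 0.800 if split 32/28. With 5 missing it is 0.795 (30/29) or 0.792 (32/27). By the normal approximation, 64 − 58 = 6 may be missing (6 / 64 = 9%).

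**Step 4: power of 64 randomised under assumed loss** (exact t-test, loss equal in both arms; the article gives no rate).

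| Loss | Complete patients | Power |
|---|---|---|
| 0% | 64 | 0.827 |
| 10% | 57.6 | 0.785 |
| 15% | 54.4 | 0.761 |
| 20% | 51.2 | 0.734 |
| 25% | 48 | 0.706 |

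**Step 5: what baseline adjustment could recover.** SPPB is measured at randomisation. If 2.17 is the SD of follow-up scores and their correlation with baseline is 0.5 (both assumed), the residual SD is 2.17 × √(1 − 0.5²) = 1.88 and d becomes 1.6 / 1.88 = 0.851. At 20% loss (25.6 per arm) power is 0.85, against 0.73 unadjusted. With an assumed correlation of 0.3, the residual SD is 2.17 × √(1 − 0.3²) = 2.07 and power at 20% loss is 0.77, so the gain depends on the correlation.

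**The case against.** The strongest reply is that nothing here harms the trial: 64 exceeds the 60 that the stated inputs require, so the count is not too low for complete data. That stands, and a reader should not infer from the mismatch that the trial is underpowered as planned.

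A second reply is that a journal article condenses the full protocol. Alpha, sidedness, the loss rate and a possible rank-test calculation are details that an article often leaves out, and 64 may already contain a margin. A rank test would be a reasonable planning choice for a 0 to 12 score. This also stands in part: 64 is undocumented, but it is not shown to be miscalculated. What remains is that the article prints an explicit pairing of 64 with 0.80 that its own inputs and named test do not yield, and uses the same 64 for needed and recruited. The point does not rest on an omission alone.

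Third, it is tempting to say that power 0.80 holds only if at most 4 of the 64 lack the endpoint. That limit depends on the exact t-test at an assumed two-sided 0.05; the normal approximation allows 6.

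Fourth, it is tempting to treat substantial loss as certain. The documents give no rate. Patients are randomised only once stable, which removes the earliest losses, and the Limitations section lists five measures to reduce the burden of the programme. Some loss is likely in this population, but its size is an assumption, and at 10% the shortfall from 0.80 is only 1.5 percentage points.

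**Conclusion.** The point holds as a reporting fault with a modest consequence for power. The stated pairing of 64 patients and power 0.80 does not follow from a difference of 1.6, SD 2.17 and the unpaired t-test: two-sided 0.05 gives 60 (58 by the normal approximation), and 64 complete patients give 0.83. The visible margin for missing endpoints is 4 to 6 patients, and power falls to about 0.76 at 15% loss and 0.73 at 20%.

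This rests on three assumptions: two-sided alpha 0.05, the reading of 1.6 as a difference between arms, and the illustrative loss rates. The second deserves care, because the article words 1.6 as an increase under CTR. If patients on RPM alone also improve, the between-group difference and the power would be smaller; the figures above do not count on that. The documents do not support a claim that 64 is too few for complete data, nor that the original calculation was wrong.

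**What to change.** Keep 64. Restate the sample size sentence so that it gives:

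- alpha and sidedness, and the test used for the calculation;
- 1.6 explicitly as the assumed between-group difference, with what 2.17 is the SD of;
- the time point to which the power applies, which the sponsor should name because the primary outcome lists several;
- the number to be analysed at that time point (60 for the t-test at two-sided 0.05), and the loss that 64 randomised therefore tolerates (about 6%), with the power at larger losses.

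If 64 came from another route, such as a rank test or a loss allowance, the sentence should say so.

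In addition, analyse follow-up SPPB adjusted for SPPB at randomisation in place of the unadjusted t-test. The baseline value is already collected, so this needs no extra patients or visits. The sponsor should state the correlation it expects, because the recovered power depends on it.

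The cost is one rewritten sentence, one changed line in the Statistical analysis section made before the data are seen, and a more candid statement of power under loss.
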